### Recruitment and Informed Consent

Primary care providers within the safety net may refer participants via email or direct messaging through the electronic health record system (Epic), and participants may also spontaneously walk-in for enrollment without a referral. Eligibility criteria are assessed via phone (for referrals) or in-person (for walk-ins) and confirmed via the electronic health record (last detectable viral load, confirmation of stimulant use disorder diagnosis, and ART regimen) before enrollment. Participants who meet the eligibility criteria are offered an enrollment visit, in which they provide informed consent and complete baseline assessments.

### Intervention

#### Description

Enrolled participants who have provided informed consent will complete baseline surveys and urine testing (Table 2), then come to the clinic (in-person) once weekly for 12 weeks. During CM visits, participants will engage in motivational interviewing (MI) and provide urine for POC tenofovir and stimulant testing, with escalating incentives for a longer duration of stimulant-free and tenofovir-containing urine (Figure 1) [27]. Of note, incentives will not require both behavioral targets to be met. For example, if a participant’s urine tests positive for tenofovir but also for cocaine, they would receive draws for tenofovir but not for stimulants. At the next study visit, the stimulant-related draws would reset to 2 (if no stimulant in urine) with a rapid reset procedure for each target behavior following a lapse in target behavior (or missing sample).

**Table 2 table2:** Assessment variables and schedule for dual-incentive contingency management in HIV primary care.

Domain and assessment			Stage of collection		
			Baseline		Study visits
**Sociodemographics**					
	Gender, age, housing status, and race or ethnicity	✓			
**Substance use history**					
	Substances currently using	✓			
	Route of use	✓			
	Overdose history, from what substances?				
	7-d timeline follow-back^a^	✓		✓	
	Severity of dependence scale^a^	✓			
**HIV history**					
	Last detectable viral load	✓		✓	
	3-point Medication Adherence Assessment^a^	✓			
	“Did you take [medication] more, less, or the same this week compared to last week?”			✓	

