### Assessment and Data Collection

All data will be captured and stored using REDCap electronic data capture tools hosted at University of California, San Francisco [35,36]. Most data metrics (described in Table 2) will be extracted from patient interviews during baseline and study visits, although viral loads will be extracted from patient’s electronic medical record.

Baseline assessments (Table 2) will extract patient variables relating to sociodemographics, substance use history, and HIV history, including HIV viral load before participation. We will also collect POC results at baseline (although no incentives will be earned from these results), perform 7-day timeline follow-back to assess baseline frequency of stimulant use, and record visit-related characteristics (length of visit and amount in US $ received through a priming draw; Multimedia Appendix 1) [37].

Visit assessments will assess recent stimulant use and ART adherence, capture POC results, and record visit characteristics (including number of incentives earned). At each visit, we will objectively assess each target behavior through POC testing (used to calculate incentives), subjectively assess stimulant use using 7-day timeline follow-back, and subjectively assess ART adherence using a 3-point Likert scale question (Table 2).

Upon intervention conclusion after 12 study visits, we will record the viral load most proximate to the patient’s last attended visit.

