### Evaluation Frameworks and Outcomes

#### Quantitative Evaluation

We will leverage the RE-AIM (reach, effectiveness, adoption, implementation, and maintenance) framework (Table 3) to quantitatively evaluate feasibility, reach, effectiveness, and intervention implementation.

Per our first study objective, we aim to evaluate the feasibility of implementing this intervention in the safety-net, ambulatory HIV care setting, which we will assess using various domains of the RE-AIM evaluation framework. Our primary outcome will be defined via engagement: 50% CM visit attendance will indicate a threshold for program feasibility. Secondary feasibility outcomes will include number of visits performed, average visit time, and monetary value earned per participant, which map to domains (Table 3). Metrics related to “reach” will assess if the proposed implementation model will be used by a diverse patient population with complex sociomedical needs (as intended), reflecting both the utility and accessibility of this program. “Effectiveness” metrics will seek to establish if the intervention modified the target behavior changes, leading to reduced stimulant use, improved ART adherence, and undetectable HIV viral loads. “Implementation” metrics will describe the costs required to start and maintain this program during the study period (8 months). Our secondary outcome is preliminary effectiveness, which we will determine using proportion of stimulant-negative and tenofovir-positive urine tests, as well as changes in HIV viral suppression before and after participation. We will report missing data and impute missing viral load data as >200 copies/mL.

**Table 3 table3:** RE-AIM (reach, effectiveness, adoption, implementation, and maintenance) framework evaluation of dual-incentive contingency management targeting antiretroviral therapy adherence and stimulant use in ambulatory HIV care.

Dimension	Question	Outcomes
Reach	Will safety-net patients living with HIV and stimulant use disorder enroll in this program? Will they return after enrollment?	Sociodemographics Substance use and HIV histories Proportion of study visits attended
Effectiveness	Will participants reduce stimulant use? Will participants improve tenofovir adherence?	Weekly point-of-care results and 7-d timeline follow-back

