### Analysis Plan

#### Quantitative Evaluation

We will analyze reach and implementation metrics (Table 3) using basic descriptive statistics. For effectiveness, we will use descriptive statistics to describe POC results, including the proportion of negative-stimulant and positive-tenofovir tests each week and cumulatively overall and the number of participants that test negative for stimulants or positive for tenofovir at least once. We will also report the average frequency of use as captured by weekly timeline follow-back and compare average use at baseline versus study visit 12 (ie, the final visit) using a paired 2-tailed *t* test. We will use the McNemar test to compare the proportion of participants with HIV viral loads less than 200 copies/mL before and after CM participation.

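### The pre-participation viral load is defined in two conflicting ways, and one of them would bias the before-after McNemar comparison towards improvement

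*Protocol article*

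**What the plan says.** All of the following is in the protocol article.

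- **Table 2, HIV history.** The one viral load row reads "Last detectable viral load". It is ticked under baseline and under study visits.
- **Recruitment and Informed Consent.** Eligibility is "confirmed via the electronic health record (last detectable viral load, confirmation of stimulant use disorder diagnosis, and ART regimen) before enrollment".
- **Assessment and Data Collection.** Baseline variables cover "HIV history, including HIV viral load before participation". This is not restricted to detectable results, and no time window is given. For the end of the intervention, "we will record the viral load most proximate to the patient’s last attended visit".
- **Evaluation Frameworks and Outcomes, Quantitative Evaluation.** Change in viral suppression is part of the secondary outcome, preliminary effectiveness. On missing values: "We will report missing data and impute missing viral load data as >200 copies/mL". The rule is not tied to one time point.
- **Analysis Plan, Quantitative Evaluation.** The McNemar test will "compare the proportion of participants with HIV viral loads less than 200 copies/mL before and after CM participation".
- **Study Population.** The adherence criterion is met by a single value over 200 copies/mL in the past 18 months, or by a reported discontinuation in that period. A participant may therefore be suppressed on the day of enrolment.

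**The concern.** A last detectable value and a latest value are different variables. The first skips any later undetectable result. For someone who enters through reported discontinuation, no value over 200 in the last 18 months is required, so the last detectable value may be older still.

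McNemar uses only the discordant pairs. If the baseline is chosen for being detectable and the end value is not, a person suppressed at both times can appear as a change to suppression, while genuine losses are hidden because the baseline was never recorded as suppressed. With no control arm, the design has nothing else that would expose a spurious gain. The pilot is also meant to inform larger trials.

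The missing-data rule raises a second, separate question. Setting a missing baseline to >200 turns anyone suppressed at follow-up into a gain.

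**Working it through.** The document gives no power, alpha or effect size for this test, and its target of about 40 participants rests on prevalence. There is no stated figure to reproduce.

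**Step 1: the possible readings.**

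| Baseline taken from | End value taken from | Consequence |
|---|---|---|
| Table 2 | Table 2 | Suppression could hardly be recorded at either time; the outcome does not work |
| Table 2 | Assessment and Data Collection | Baseline selected for being detectable, end value not; biased towards improvement |
| Assessment and Data Collection | Assessment and Data Collection | No tilt from the definition |

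**Step 2: how few participants matter.** With k gains and no losses, the exact two-sided McNemar p-value is 2 × 0.5^k.

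- k = 5: 2 × 0.03125 = 0.0625
- k = 6: 2 × 0.015625 = 0.031
- k = 8: 2 × 0.00390625 = 0.0078

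Six participants are 6/40 = 15% of the target, or 6/37 = 16% of those recruited. The count of six is an illustration; the documents do not say how many participants were suppressed at entry.

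**Step 3: simulation with no true change.** Exact two-sided McNemar test at 0.05, N = 37 (the number recruited), 20,000 runs. The following are assumptions and are not in the documents: true suppression is 30% or 50% at both times, 70% of those suppressed stay suppressed, and q is the share of truly suppressed baselines recorded as >200 because the last detectable value is used. Each cell gives the result at 30% / 50% suppression.

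| q | Missing baseline | Missing follow-up | False improvement | False worsening |
|---|---|---|---|---|
| 0 | 0 | 0 | 0.7% / 1.2% | 0.8% / 1.1% |
| 0.5 | 0 | 0 | 34% / 62% | 0% / 0% |
| 0.5 | 0 | 20% | 12% / 23% | 0% / 0% |
| 1 | 0 | 0 | 98% / 100% | 0% / 0% |
| 1 | 0 | 20% | 91% / 100% | 0% / 0% |
| 1 | 0 | 40% | 67% / 98% | 0% / 0% |

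The q = 1 rows are easy to check by hand. Everyone suppressed at follow-up is a gain and no loss is possible. With complete data that gives 0.30 × 37 = 11.1 or 0.50 × 37 = 18.5 expected gains, well above six.

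**Step 4: the imputation rule alone (q = 0).**

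| Missing baseline | Missing follow-up | False improvement | False worsening |
|---|---|---|---|
| 10% | 0 | 2.3% / 4.1% | 0.3% / 0.2% |
| 20% | 0 | 5.6% / 11.7% | 0.1% / 0.1% |
| 0 | 20% | 0.1% / 0.0% | 5.7% / 10.9% |
| 10% | 10% | 0.9% / 1.2% | 0.8% / 1.2% |
| 5% | 20% | 0.2% / 0.2% | 3.7% / 7.0% |

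The rule pushes in opposite directions at the two ends. Equal missingness cancels, and more missing follow-ups than baselines makes it conservative on balance.

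**The case against.** The strongest reply is that the text governing the comparison never uses the detectable-only term. Assessment and Data Collection gives an unrestricted pre-participation value, and the Analysis Plan speaks only of viral loads before and after. The eligibility check is a natural place for a last detectable value, since one value over 200 in 18 months can qualify a person, so it does not show that this value enters the test. Table 2 ticks the same row at study visits, where a literal reading would defeat the plan's own outcome; that suggests a loose label for the latest result. All of this stands. It makes the tilt conditional, but the only variable the assessment schedule names is still the wrong one for the test.

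It also stands that detectable does not mean over 200. A detectable value below 200 still counts as suppressed, so q = 1 is an upper bound. The counts and suppression rates used above are assumed.

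A reader might infer that the planned test is tilted towards improvement as written, and that the imputation rule adds to the tilt. The documents support neither. One of the two baseline definitions is unbiased, and the imputation also turns missing follow-ups into failures. Because viral load history is checked in the health record before enrolment, frequent missing baselines are not an obvious expectation.

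**Conclusion.** The point holds as an unresolved conflict of definition. If the Table 2 item serves as baseline against the nearest-in-time end value, the McNemar comparison is biased towards improvement. Under the assumptions above, with no missing data, the false-improvement rate is 34% to 62% when half of the suppressed baselines are misrecorded and 98% to 100% when all are, against 0.7% to 1.2% with a correct baseline. If Table 2 is used at both times, the outcome cannot be measured. If the text in Assessment and Data Collection is used throughout, the definition causes no bias.

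The imputation rule is a smaller, separate matter. It is defensible for a missing follow-up and unsuitable for a missing baseline, and its net direction is unknown without the missingness at each time.

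This is worth correcting, but it is not critical to the trial. It affects a secondary outcome of a single-arm pilot; the primary outcome, visit attendance against a 50% threshold, is untouched.

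**What to change.** 1. In Table 2, replace the viral load item with the most recent viral load of any result on or before enrolment, with its date. Use it as the McNemar baseline, in line with Assessment and Data Collection.
2. Keep the last detectable value for the eligibility check only.
3. Limit the >200 imputation to missing follow-up values. Exclude pairs with no baseline from the main comparison, and add a sensitivity analysis that sets those baselines to <200.
4. The Results section reports that the quantitative analysis concluded in June 2025. The sponsor should therefore confirm which baseline was used, and rerun the comparison if it was the last detectable value.

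**Cost.** One field from the same health record, plus a few lines of wording. There will be slightly fewer pairs, and fewer participants will be able to count as improved. Keeping the imputation for follow-up leaves the comparison conservative when follow-up values are missing.

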**Point-of-care results**					
	Tenofovir detected	✓		✓	
	Stimulants detected	✓		✓	
	Other substances detected	✓		✓	
**Visit characteristics**					
	Length of visit	✓		✓	
	Number of incentives earned			✓	
	Amount earned	✓		✓	

^a^Use of the validated assessment tool.

**Figure 1 figure1:**
[figure not shown]
Intervention description. ART: antiretroviral therapy; NEG: negative; POC: point of care; POS: positive; SCID-5: Structured Clinical Interview for DSM-5.

All visits will occur in-person in clinic on the same day of the week. Participants will be invited to drop-in for study appointments anytime during clinic hours (9 AM to 5 PM). Visits are estimated to last approximately 20 minutes.

The following key tenets of CM will be adhered to: (1) frequently monitoring the behavior of interest (eg, stimulant use and adherence assessed weekly); (2) tangible, immediate positive reinforcement after confirmation of behavior of interest (eg, POC testing allows for immediate provision of incentives if indicated); and (3) positive reinforcement (ie, incentives) withheld if behavior of interest is not demonstrated [21]. We will use the prize method for reinforcement provision (also known as the “fishbowl method,” established by CM authority [name]), in which participants earn an escalating number of draws from a fishbowl containing paper slips with variable monetary value [28,29]. As specified by distribution of paper slips, patients have a 50% chance of drawing a monetary incentive and 50% chance of drawing an affirmation with an encouraging message (no monetary value; Figure 1). In keeping with this method, participants will receive a “priming draw” at their enrollment visit, in which they draw from the fishbowl until they receive a monetary prize, regardless of their POC results. If a participant misses a visit or does not provide evidence for the target behaviors, the number of draws related to that behavior resets to zero (ie, stimulant positive urine will reset stimulant-related draws to zero).

#### Theory for Formative Components

To customize the CM intervention to our target safety-net population, we used the Behavior Change Wheel framework to identify population-specific barriers to behavior change and created intervention components to address these barriers (Table 1). These formative components are discussed in the subsequent sections.

#### Incentivizing Stimulant Use Reduction

We hypothesize that incentivizing stimulant use reduction rather than abstinence will be acceptable to our target safety-net population with comorbid stimulant use disorder and HIV. One challenge to incentivizing stimulant use reduction is that no POC tests measure quantitative levels of cocaine or methamphetamine and thus cannot determine if one positive result represents a reduction or increase in use compared to another positive result. To overcome this challenge, we will assess stimulant use once weekly using POC tests with an approximate 4-day detection window. This would theoretically allow participants to continue using substances some days of the week, but still test negative for stimulants on POC tests if they do not use in the days preceding testing. Given that (per inclusion criteria), participants endorse using stimulants most days of the week (if not daily), we theorize that a negative result will constitute a true sign of use reduction.

#### Offering Drop-In, Individual Visits

The need to adhere with scheduled clinic appointments is a frequently cited barrier to engagement in care for vulnerable populations, including people living with HIV. Emerging models of care have shown that offering low-threshold, drop-in visits without an appointment can circumvent this barrier to achieve robust improvement in care engagement and target health outcomes; one such model is demonstrated in the POP-UP clinic, one of this study’s 2 host clinics, wherein more than 50% of enrolled, viremic patients experiencing homelessness achieved viral suppression within 6 months [30,31]. In keeping with low-barrier principles, we expect that offering drop-in visits will optimize engagement for safety-net patients with complex psychosocial factors.

#### Incorporating MI

MI is a psychosocial interviewing technique that aims to enhance intrinsic motivation by eliciting statements that amplify and reinforce a patient’s commitment for behavioral change [32]. Several meta-analyses have shown that interventions using MI have had some effect on reducing substance use (including stimulants) and that pairing MI with CM interventions may lead to more durable behavior change [33]. In addition, integrating MI into CM study visits can help promote relationship building between patients and CM providers, which we expect will be particularly important for cultivating trust among patients with negative past health care experiences related to substance use or HIV-related stigma [33].

### CM Provider and Training

One CM provider will be trained to lead all CM activities with supervision by the principal investigator, an addiction medicine specialist. Training includes (1) POC device training; (2) completing the free, virtual “Contingency Management Overview Training” offered by the Recovery Incentives Program at the University of California, Los Angeles; (3) addiction medicine–specific intensive MI through a 2-day training workshop [34].

### Materials

At enrollment, participants will receive a visual schema describing the incentive structure and indicating where or when they may come in for CM visits (Multimedia Appendix 1).

The materials required for conducting study visits include fishbowl with paper slip incentives (Figure 1), stimulant POC tests, tenofovir POC tests (Figure 2), gift cards, and sign-out sheets (to confirm receipt of gift cards and record barcodes, as required by our funding mechanism), and timeline follow-back form (Multimedia Appendix 1).

The number of incentives earned during each visit will be automatically calculated via REDCap (Research Electronic Data Capture; Vanderbilt University; calculated field using special functions) after input of POC results.

**Figure 2 figure2:**
[figure not shown]
Novel point-of-care urine tenofovir test.

### Assessment and Data Collection

All data will be captured and stored using REDCap electronic data capture tools hosted at University of California, San Francisco [35,36]. Most data metrics (described in Table 2) will be extracted from patient interviews during baseline and study visits, although viral loads will be extracted from patient’s electronic medical record.

Baseline assessments (Table 2) will extract patient variables relating to sociodemographics, substance use history, and HIV history, including HIV viral load before participation. We will also collect POC results at baseline (although no incentives will be earned from these results), perform 7-day timeline follow-back to assess baseline frequency of stimulant use, and record visit-related characteristics (length of visit and amount in US $ received through a priming draw; Multimedia Appendix 1) [37].

Visit assessments will assess recent stimulant use and ART adherence, capture POC results, and record visit characteristics (including number of incentives earned). At each visit, we will objectively assess each target behavior through POC testing (used to calculate incentives), subjectively assess stimulant use using 7-day timeline follow-back, and subjectively assess ART adherence using a 3-point Likert scale question (Table 2).

Upon intervention conclusion after 12 study visits, we will record the viral load most proximate to the patient’s last attended visit.

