### Study Population and Inclusion and Exclusion Criteria

Recruitment, enrollment, and study procedures will occur at Ward 86, with targeted recruitment from the aforementioned clinics. We aim to recruit participants living with HIV who (1) are on tenofovir-based ART regimens, (2) are diagnosed with severe stimulant use disorder (according to the *Diagnostic and Statistical Manual of Mental Disorders, Fifth Edition* criteria, measured with the Structured Clinical Interview for DSM-5, using at least near daily), (3) have suboptimal ART adherence (defined as at least one instance of HIV viral load over 200 copies/mL in the preceding 18 months or reporting periods of discontinuation within last 18 months), (4) are interested in reducing frequency of stimulant use and improving ART adherence, and (5) speak either English or Spanish [26]. On the basis of the estimated prevalence of comorbid stimulant use disorder and HIV within our target safety net, we aim to recruit approximately 40 participants.

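### The 'after' viral load may be drawn before enrolment, so one measurement can serve as both before and after for participants who stop early

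*Protocol article*

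**What the plan says.** All of this is in the protocol article.

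- **Source.** Under Assessment and Data Collection, "viral loads will be extracted from patient’s electronic medical record". No study blood draw is described. Table 2 ticks a viral-load item at baseline and at study visits but gives no test schedule or window.
- **Before value.** The same section includes in the baseline data "HIV history, including HIV viral load before participation".
- **After value.** "Upon intervention conclusion after 12 study visits, we will record the viral load most proximate to the patient’s last attended visit".
- **Missing values.** Under Evaluation Frameworks and Outcomes, Quantitative Evaluation: "We will report missing data and impute missing viral load data as >200 copies/mL".
- **Test.** Under Analysis Plan, Quantitative Evaluation, the McNemar test is used to "compare the proportion of participants with HIV viral loads less than 200 copies/mL before and after CM participation".
- **Who enters.** Suboptimal adherence means "at least one instance of HIV viral load over 200 copies/mL in the preceding 18 months or reporting periods of discontinuation within last 18 months". Eligibility is "confirmed via the electronic health record (last detectable viral load, confirmation of stimulant use disorder diagnosis, and ART regimen) before enrollment".

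**The concern.** The nearest value can lie on either side of the anchor, and the anchor is the last visit the participant attended. For someone who attends once or twice, the nearest result in the record may be the one taken before enrolment. That person then contributes a pair with no information about change, although the analysis is described as comparing status before and after the programme.

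The rule also weakens the plan's own safeguard. Without a window, an after value is missing only if the record holds no viral load at all. Since the record is checked for viral load before enrolment, that should be rare. A dropout who was suppressed at baseline would then be reported as suppressed after the programme, where the missing-value rule would have counted a failure.

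Early stopping is foreseeable. The feasibility threshold is 50% attendance, and the interview plan reserves places for people who attended fewer than half the visits.

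**Working it through.** The documents give no effect size, power, dropout rate, testing interval or baseline suppression rate for this comparison, so there is no stated figure to reproduce. The check is by logic first and then by illustration.

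**Step 1. Who is classified differently?** Take a participant with no post-enrolment result whose before value is the latest pre-enrolment one.

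| Baseline status | Nearest-value rule | Missing counted as >200 | Difference |
|---|---|---|---|
| Suppressed | suppressed, suppressed | suppressed, not suppressed | one worsened pair removed |
| Not suppressed | not, not | not, not | none |

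Against the plan's missing-value rule the effect runs one way, and only through participants suppressed at baseline. Such participants can exist, because eligibility accepts a raised value at any time in 18 months, or a reported interruption instead.

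**Step 2. How often would the nearest value predate enrolment?** Assume routine tests every T weeks at random phase and a last visit at week L. The nearest test is then uniform within T/2 either side of L, so

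P = max(0, T/2 − L) / T.

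| T (weeks) | L = 1 | L = 3 | L = 6 | L = 12 |
|---|---|---|---|---|
| 8 | 3/8 = 37.5% | 1/8 = 12.5% | 0 | 0 |
| 13 | 5.5/13 = 42% | 3.5/13 = 27% | 0.5/13 = 4% | 0 |
| 26 | 12/26 = 46% | 10/26 = 38% | 7/26 = 27% | 1/26 = 4% |

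**Step 3. How many participants?** Use the 37 recruited (Results). Assume 10 stop by week 3 and 40% of them were suppressed at baseline: 10 × 0.4 = 4.

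- Lowest for 13- to 26-weekly testing: 4 × 0.269 = 1.1 participants; 1.1/37 = 2.9 points.
- Highest: 4 × 0.462 = 1.8 participants; 1.85/37 = 5.0 points.
- If all 10 carry baseline over: 4/37 = 10.8 points.
- With 8-weekly testing and a last visit at week 3: 4 × 0.125 = 0.5 participants; 0.5/37 = 1.4 points.

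These figures assume that none of the affected participants has a later usable result. Where one exists, the difference from the missing-value rule disappears, and using that result could move the comparison either way.

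**Step 4. Can so few records matter to the test?** Assume 10 improved and 2 worsened pairs among 37. The exact two-sided McNemar p is 2 × P(X ≥ 10), with X binomial (improved + worsened, 0.5).

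| Worsened pairs restored | Improved vs worsened | Net change | p |
|---|---|---|---|
| 0 | 10 vs 2 | 8/37 = 21.6 points | 0.039 |
| 1 | 10 vs 3 | 7/37 = 18.9 points | 0.092 |
| 2 | 10 vs 4 | 6/37 = 16.2 points | 0.18 |
| 4 | 10 vs 6 | 4/37 = 10.8 points | 0.45 |

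The article states no significance level. At a conventional 0.05, one or two records could change the reading in this example.

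**The case against.** The best defence is that the sentence should not be read alone. The baseline value is described as preceding participation, the comparison is described as before and after, and a missing-value rule makes sense only if after values can be missing. On that reading a pre-enrolment result could never be the after value. This shows the intention, and it is a fair point. It does not repair the rule: the only instruction for choosing the value is nearness to the last attended visit, and whoever extracts the records would follow that.

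It can also be said that windows and the definition of missing are often left to a fuller document. True for a window alone. Here, however, the article states a selection rule, and that rule can return the wrong measurement.

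Several other points stand:

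- Anchoring at the last attended visit captures status at the end of actual exposure. Anchoring at week 12 answers a different question, and the choice is partly preference.
- A reader might infer that after values could be drawn many months late. The article says the value is recorded when the intervention ends, which on its face limits this.
- A reader might infer that dropouts in general become unchanged pairs where they should be failures. Step 1 shows this only for those suppressed at baseline.
- Results reports that the 37 recruited patients finished 12 weeks. That may mean elapsed time, not attendance to the last week, but it gives no support for a particular number of early dropouts.

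**Conclusion.** The point holds as a defect in a stated rule and should be corrected. The selection rule allows one measurement to be both before and after, conflicts with the comparison the analysis plan describes, and leaves the missing-value rule little to act on. That last part is inference from the wording and the pre-enrolment record check; no count of missing values is given.

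The likely size is modest: about 1 to 2 participants, or 3 to 5 percentage points of 37, on the assumptions in the working. A reader might take the 11-point figure, or the matching 10/37 = 27% of pairs fixed by construction, as the expected effect. The documents do not support that: both figures require every one of 10 assumed dropouts to have the baseline result as the nearest one.

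Nor does the point undermine the trial as a whole. The primary outcome is visit attendance, which is untouched. Viral suppression is one part of a secondary, preliminary effectiveness outcome in a single-arm pilot. It is, however, one of only two comparisons given a hypothesis test, and the pilot is meant to inform larger trials.

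**What to change.** Revise the extraction rule as follows:

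1. The after value must be drawn after enrolment.
2. The baseline measurement may not also serve as the after value.
3. The after value must lie in a bounded window around a stated time point, for example 12 weeks after enrolment. The window's width is for the investigators to choose and justify.
4. Anyone without a value in the window is coded missing, so that the >200 copies/mL rule applies.
5. Report the number imputed and show the complete-case result alongside.

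Results states that the quantitative analysis had concluded by June 2025, so this should be labelled a post hoc correction or sensitivity analysis and shown beside the result under the existing rule.

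The cost is re-extraction for about 37 records and one further table. The downside is that more values will be classed as missing, so suppression after the programme may look lower.
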